**Figure 1 figure1:**
[figure not shown]
Flowchart of study participation. CHUM: Centre hospitalier de l’Université de Montréal.

### Blinding and Allocation Concealment

Eligible patients will first be approached by telephone by a member of the research team when the preoperative clinical appointment is booked. During the preoperative clinical assessment, patients will receive both oral and written information on the study by a research nurse not involved in patient care. Patients will be included in the trial only after a research nurse has obtained written informed consent.

All included patients will be electronically randomized into the intervention group or the control group. Randomization will be performed by one of the investigators using the MedSharing Randomizer for Clinical Trial web application. The 2 groups will be balanced at a 1:1 ratio. Patients who are recruited but do not receive surgery within the study time frame will be secondarily excluded.

The study will be single-blinded. Statisticians will assess the primary and secondary outcomes, blinded to the randomization group. However, due to the nature of the intervention, neither the patients nor the care providers will be blinded to the randomization.

### Recruitment and Intervention

During the recruited patients’ visits to the preoperative clinic, they will benefit from safe and restricted web access to the LeoMed telehealth platform. After confirmation of the date of surgery, patients will be allocated according to the randomization list to the intervention group or the control group.

### Intervention Group

The day before their surgery, patients will receive an email or SMS notification encouraging them to access the LeoMed platform. The platform prompts patients to click on links that direct them to the digital portal of the CHUM website, where all health sheets describing the perioperative pathway are published and grouped together, and preoperative psychological empowerment video resources are available that have been specifically created with the help of the CHUM communications service.

Postoperatively, notifications will be sent to the participants every day during the first 4 days. These notifications will direct patients to online forms assessing their medical condition. The questionnaires used are derived from the Brief Pain Inventory [18] and the Institut national de santé publique du Québec (INSPQ; Quebec Public Health Expertise and Reference Center in English) [19], which suggests using a simple questionnaire with 4 items for identification of surgical site infections. The items include redness at the surgical site, presence of pus at the surgical site, fever, and wound pain.

The LeoMed platform will automatically classify patients’ responses using an artificial intelligence algorithm and generate alerts on the home page. The home page is displayed on a giant screen on CHUM’s telehealth service, which will offer tailored support according to patients’ clinical need.

Health support will be provided by CHUM’s telehealth service, which comprises a team of 50 nurses. This department is a 24/7 call center that manages many telecare platforms dedicated to remote patient support for various medical specialties. All the staff of this service are trained in new technologies. Their mission is to provide health care remotely and to coordinate the interventions of different medical and paramedical personnel within the hospital. Specifically for this project, patient responses appear on a giant screen in the main open space where the CHUM telehealth service nurses work. In the event of an alert, a nurse will contact the patient within a maximum of 8 hours and provide appropriate care.

On postoperative day (POD) 15 and 30, the LeoMed platform will send a follow-up form that aims to evaluate all indicators considered in the medicoeconomic analysis. All the indicators are detailed in Table 1.

**Table 1 table1:** Schedule of enrollment, interventions, and assessments.

Timepoint			Preoperative consultation		At the confirmation of the date of surgery		Preoperative day 1		POD^a^ 1		POD 4		POD 7		POD 15 and POD 30
**Enrollment**															
	Eligibility screening	✓													
	Informed consent	✓													
	Allocation			✓											
**Intervention**															
	Intervention group	✓				✓		✓		✓		✓		✓	
	Control group	✓												✓	
**Assessments on** **the LeoMed platform**															
	Quality of life (EQ-5D-5L visual analogue scale)	✓												✓	
	Unplanned readmissions													✓	
	Unplanned visits (eg, family doctor, walk-in clinic)													✓	
	Emergency department visits													✓	
	Calls to CHUM^b^ online support													✓	
	Calls to the Quebec health information line													✓	
	**Assessments from the electronic medical record system**														
	Same-day cancellations							✓							
	Calls to CHUM online support													✓	

^a^POD: postoperative day.

^b^CHUM: Centre hospitalier de l’Université de Montréal.

### Control Group

Participants assigned to the control group will be followed up according to usual care, which consists of a telephone call the day before the procedure as a reminder of safety instructions. Postoperative follow-up is not standardized and remains specific to each surgical specialty. Access to a limited version of the LeoMed platform will also be given to these participants during the preoperative clinic visit. This version includes a preoperative questionnaire and follow-up forms at POD 15 and POD 30 that are identical to those received by the intervention group and collect the indicators considered in the primary analysis (Table 1). Like the patients in the intervention group, the control patients will have 24/7 access to the provincial or CHUM health information lines, if needed.

### Primary Outcome

The primary outcome will be the cost-effectiveness of the LeoMed telecare platform deployment assessed by its direct costs, including unanticipated cancellations on the day of surgery due to preoperative instructions not being followed, calls to the local CHUM health information line, calls to the Quebec health information line (ie, 811), visits to the emergency department, and unplanned readmissions or medical visits (to family doctors or outpatient clinics) for problems related to the procedure within the first 30 days after the procedure.

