**Methods:**

This study is a single-center, single-blinded, 2-group randomized controlled trial. One thousand patients aged over 18 years with internet access who are scheduled to undergo ambulatory surgery will be enrolled and randomized either to follow a perioperative path that includes a patient-tailored perioperative digital app via the LeoMed telecare platform for 1 month or to follow the standard of care, which does not offer personalized digital support. The primary outcome will be to evaluate the cost-effectiveness of the telecare platform, assessing direct costs from factors such as unanticipated cancellations on the day of surgery due to preoperative instructions not being followed, calls to the local health information line, calls to the provincial health information line, emergency department consultations, unplanned readmissions, or medical visits for problems related to the surgical procedure within the first 30 days after the intervention. The secondary outcome will be to evaluate cost utility using a questionnaire assessing quality-adjusted life years. A blinded independent research team will analyze outcomes. All data will be analyzed according to the intention-to-treat principle. A sample size of 500 subjects in each group was calculated to detect a 21% reduction in postoperative complications with a power of 90%. This study has been approved by the ethics board of Centre hospitalier de l’Université de Montréal (University of Montreal Health Centre). No employee of LeoMed was involved in the study conception, and none will be involved in either data collection or analysis.

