The department of anesthesiology at the Centre hospitalier de l’Université de Montréal (CHUM; University of Montreal Medical Center in English), in collaboration with LeoMed, has developed a dedicated digital smart solution specifically designed to offer personalized perioperative support and follow-up via a telecare platform that can easily be installed on any smartphone. We hypothesize that the implementation of this telehealth platform at CHUM will (1) reduce the rate of unanticipated cancellations of elective surgeries through better preoperative information and communication, (2) improve quality of life 30 days after surgery due to faster and better recognition of postoperative complications, and (3) reduce the rate of emergency department or unplanned medical visits and unnecessary calls to the health information line, as well as reduce unplanned hospital readmissions, through more personalized health support. Our overall conjecture is that including the LeoMed patient-tailored telecare platform in the perioperative day-surgery pathways of patients will improve the medicoeconomic impact of care services compared with standard care. The main objective of this study is to assess the cost-effectiveness of the LeoMed platform, and our secondary objective is to perform a cost-utility analysis.

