### Secondary Outcome

The secondary outcome considered for the cost-utility analysis will be quality-adjusted life years (QALYs). According to a recent update of the guide for economic evaluation published by the French National Authority for Health [20], the EQ-5D-5L visual analog scale (VAS) is the preferred measure used to assess quality of life and to derive utility values for use in health technology appraisals. It will be assessed at POD 30 and compared with the preoperative baseline [21]. The EQ-5D-5L VAS is a questionnaire that is well validated. It includes 5 dimensions, each describing a different aspect of health: mobility, self-care, usual activities, pain/discomfort, and anxiety/depression. Patient satisfaction with care services will also be assessed.

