### Data Analysis

Data analysis will be performed by a team of researchers at the École des Hautes Études Commerciales in Montreal, Quebec, using SPSS (version 28; IBM Corp). All data will be analyzed according to the intention-to-treat principle. Descriptive statistics will be reported as frequencies and proportions for categorical data and means and standard deviations for continuous variables. Demographic data for the 2 groups of patients will be compared using the Mann-Whitney *U* test (for ordinal data), the chi-square test (for nominal data), and a 2-tailed *t* test (for continuous data).

Considering the Canadian guidelines for the economic evaluation of health technologies [22], the perspective of the health care system will be privileged in this study. Specifically, 2 main types of analyses will be carried out. First, all interventions in both groups related to surgery (calls to the provincial or CHUM information lines, visits to the ambulatory unit, hospital readmissions, and visits to the emergency department) will be recorded during the study to perform the cost-effectiveness analysis. Second, a cost-utility analysis will be conducted to quality-weight each effectiveness outcome measured in QALYs. QALYs will be calculated as life with the health state under study multiplied by the utility associated with that health state. CHUM’s internal data will be used to determine the cost of health care staff and the average cost of an emergency room visit for the clientele concerned in fiscal year 2019-2020. For hospitalizations, we will use the average costs calculated according to the American diagnosis-related groups method, which was applied at CHUM in 2019-2020. Technology costs will be estimated based on license prices in effect at the time of the study and amortized on a straight-line basis over a 5-year period. All calculations will be in Canadian dollars. Last, patient satisfaction with care services will be measured in both groups at the end of the trial using Likert scales adapted from Sicotte et al [23]. This protocol follows the SPIRIT (Standard Protocol Items: Recommendation for Interventional Trials) 2013 Statement for trial protocols [24].

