### Sample Size

There are very few studies that have examined the effects of digital solutions for personalized support and follow-up for patients undergoing day surgery. We based our sample size calculations on Jaensson et al [25], assuming that a better postoperative recovery (ie, decreased symptoms and complications) should reduce the number of postoperative calls to the health information line, visits to the emergency department, unplanned readmissions and medical visits, and the associated costs (our primary outcome). Jaensson et al [25] reported better recovery (based on the global Swedish Web Version of the Quality of Recovery [SwQoR] score) in an intervention group (ie, day surgery patients using a recovery assessment mobile phone app) compared with a control group (standard care) on POD 7 (effect size 0.21; *P*<.001). With a significance level of .05 and a statistical power of .90, G*Power (Heinrich Heine University) generated a group size of 357. To allow for a 20% rate of loss to follow-up and protocol deviations, we thus aim to recruit 500 patients per arm. In the third quarter of 2019, CHUM provided nearly 630 outpatient surgical stays per month on average. Considering 70% of patients should be eligible for the study [26], it will take about 12 months to recruit 1000 patients.

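### The primary outcome is labelled cost-effectiveness but defined by direct costs, and no effect measure is designated to set against them

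*Protocol article*

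**What the plan says.** The Introduction sets the aims: "The main objective of this study is to assess the cost-effectiveness of the LeoMed platform, and our secondary objective is to perform a cost-utility analysis". The Objective paragraph of the Abstract adds a directional hypothesis, that the platform will lower the medical costs of the day-surgery pathway.

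The Primary Outcome section turns the main aim into an endpoint: "The primary outcome will be the cost-effectiveness of the LeoMed telecare platform deployment assessed by its direct costs". The Abstract uses the same construction: "The primary outcome will be to evaluate the cost-effectiveness of the telecare platform, assessing direct costs from factors such as unanticipated cancellations". Both go on to list resource-use events.

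The Data Analysis section says that surgery-related calls, visits and readmissions in both groups "will be recorded during the study to perform the cost-effectiveness analysis". It describes unit costs for staff, emergency visits, hospitalisation and technology, and takes the health care system's perspective. For the second analysis it says that "a cost-utility analysis will be conducted to quality-weight each effectiveness outcome measured in QALYs". The Secondary Outcome section places the QALY there: "The secondary outcome considered for the cost-utility analysis will be quality-adjusted life years (QALYs").

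The Sample Size section gives a list of calls, emergency visits, readmissions and medical visits, and ends it with "and the associated costs (our primary outcome").

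**The concern.** A cost-effectiveness analysis sets a difference in cost against a difference in effect. Here the endpoint that carries the cost-effectiveness label is specified through costs, and the specification never says which quantity is the effect. Taken literally, it yields a comparison of costs between arms.

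That matters because the result could fall either way. Only the intervention arm receives the early postoperative forms, the alerts and nurse contact after an alert, and technology and staff costs are to be counted. The platform could therefore cost more in total even if it prevents some events. The primary result would then need a stated effect to show what the extra spending buys. If the platform costs less, a claim of cost-effectiveness still needs a stated effect that is shown to be no worse. The Discussion says that the trial is meant to fill a gap in the economic evidence available to public payers, so the meaning of the headline result should be fixed in advance.

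**Working it through.** No figure in the plan bears on this point, so the check is a reading of the sections against one another.

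**Step 1. Which quantity could be the effect in the primary analysis?**

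| Candidate | Where it appears | Designated as the primary effect? |
|---|---|---|
| Event counts | Primary Outcome, Table 1, Data Analysis | No. They are introduced as direct costs; none is selected and no combining rule is given |
| QALYs | Secondary Outcome, Data Analysis | No. Assigned to the secondary cost-utility analysis |
| Recovery score | Sample Size, from an earlier trial of a recovery app | No. Not among the assessments in Table 1 |
| Postoperative complications | Abstract, sample size sentence | No. Not listed as an outcome of this trial |

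No incremental ratio, net benefit or other joint summary is named for the primary analysis either. The phrase about each effectiveness outcome in Data Analysis does not settle the matter. It may point back to the events listed in the sentence before it, but it does not identify them as effects, and it occurs in the description of the QALY analysis.

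**Step 2. What can a difference in total cost establish alone?**

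| Incremental cost | Effect better | Effect worse or equal |
|---|---|---|
| Lower | Platform dominates | Saving, at a loss of effect or none |
| Higher | Trade-off: extra cost per unit gained | Platform not worthwhile |

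The cost difference fixes the row. Choosing the column needs a designated effect. The cost-reduction hypothesis concerns only the row, so the planned data can answer it. The main objective in the Introduction needs both.

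**Step 3. How open is the choice of effect?** The Primary Outcome section names six event types: avoidable same-day cancellation, call to the hospital line, call to the provincial line, emergency visit, readmission and unplanned medical visit. An effect of the form 'free of any event in a chosen set' can be built from any non-empty subset, which gives 2^6 − 1 = 64 − 1 = 63 definitions. This leaves aside the choice between counts and proportions and any weighting. The figure describes the freedom left open. It is not an error rate.

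The lists themselves also differ. The Data Analysis list omits same-day cancellations and speaks of ambulatory-unit visits, where the Primary Outcome section has family doctors and outpatient clinics. Technology cost appears under Data Analysis but is not itemised under Primary Outcome.

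**The case against.** The best reply is that the events are the effects. The Introduction hypothesises lower rates of cancellation, emergency and unplanned visits, calls and readmission. The same events are recorded in both arms on identical day 15 and day 30 forms, with cancellations taken from the medical record. Counts and unit costs enter as separate inputs, so a cost per event avoided can be computed. This stands in large part: the plan does collect effects in natural units. It does not say which of them is the effect, and it introduces all of them as components of direct cost.

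Two stronger readings are tempting, and the article does not support them.

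- A reader might infer that the main objective cannot be answered at all, or that a cost-effectiveness conclusion would be unfounded whichever way costs go. That goes too far. Emergency visits, readmissions and unplanned visits for procedure-related problems are adverse patient outcomes inside the primary list, and quality of life at day 30 is a planned secondary measure. Deterioration could show in either.
- A reader might take the Sample Size section to say outright that the primary outcome is cost alone. Its parenthesis, "and the associated costs (our primary outcome"), can cover the whole preceding list of events as well as their costs. The sentence is ambiguous.

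It can also be said that the analysis plan or full protocol will supply the detail. That holds for interval methods, resampling and modelling of costs, and nothing here rests on their absence. It does not hold for the identity of the primary outcome: the article defines it in its own section, and the definition does not match the label.

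**Conclusion.** The point holds in a limited form. The primary outcome, as defined in the Abstract and the Primary Outcome section, is a direct-cost outcome under a cost-effectiveness label. It can test whether costs fall. It does not by itself support a conclusion on cost-effectiveness, because no effect and no incremental summary are designated, and the one effect explicitly tied to costs sits in a secondary analysis. Usable effects are collected, but with none chosen, the effect could be picked once the results are known.

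The size is structural: the data remain usable, and what is affected is the meaning of the headline result. No money value or loss of power can be derived. It would be wrong to illustrate the effect by applying the Abstract's 21% reduction to the 9.4% emergency return rate in the Introduction, since the Sample Size section shows that 0.21 is an effect size on a recovery score.

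The conclusion rests on the article alone and assumes that no fuller document has already designated the primary effect.

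**What to change.** Choose one of two routes and carry the wording through the Abstract, Introduction, Primary Outcome, Data Analysis and Sample Size sections.

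(a) Rename the primary outcome as the between-arm difference in mean total 30-day direct cost per patient, including platform cost. Reserve the term cost-effectiveness for the joint analysis of cost and QALYs. This is the simpler route and fits the stated hypothesis.

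(b) Keep the label and name one effect already collected, for example the proportion free of any emergency visit, readmission or unplanned visit to day 30. Report incremental cost and incremental effect jointly, and state openly that the same events also enter the cost side.

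Under either route, use one list of cost items throughout and state the analysed population. Data Analysis promises intention to treat. The Population section, however, allows exclusion after randomisation for conversion to inpatient stay or last-minute postponement, and the Blinding and Allocation Concealment section excludes patients not operated on within the study period. These statements must be reconciled, particularly because a postponement exclusion could remove patients whose same-day cancellation is itself a primary outcome event.

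The cost is an amendment with the committee and ethics approvals foreseen under Ethics Approval. Recruitment began in August 2022, and 142 of the planned 1000 patients (14.2%) were enrolled by 31 October 2022, so the change should be dated and made before any comparison by arm. Neither route calls for a new assessment, although reconciling the population may require follow-up of patients who would otherwise be excluded. Route (a) carries a less ambitious label; route (b) accepts overlap between the cost and effect sides.

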### Data Collection

Data for primary and some secondary outcome measures will be collected from the LeoMed platform until POD 30, with the exception of same-day cancellations. These data will be collected on POD 1 from the electronic medical record (EMR) system by 1 member of the research team (Table 1). In the absence of spontaneous responses from patients at POD 30 or if the forms are incomplete, patients will be called by one of the research assistants to assess the indicators included in the cost-effectiveness and cost-utility analyses. If a postoperative event is reported via the form, the patient will also be contacted personally by telephone.

For each patient, data will be systematically registered and archived on a local secure server. Patients will be identified using a unique numeric code, and all patient data will be anonymized to ensure confidentiality. All data will be extracted and cross-referenced with Oacis (Telus Health), the EMR system used at CHUM.

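### The primary cost outcome depends on judging why events happened, but the stated blinding covers only the statisticians, so arm-dependent attribution or ascertainment can bias it in either direction.

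*Protocol article*

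**What the plan says.** All references are to the protocol article.

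- **Primary Outcome** attaches causal conditions to what is costed. Cancellations count when they are "unanticipated cancellations on the day of surgery due to preoperative instructions not being followed". Readmissions and medical visits count "for problems related to the procedure within the first 30 days after the procedure".
- **Data Analysis** says that what will be recorded for the cost-effectiveness analysis is "all interventions in both groups related to surgery", and its list includes information-line calls and emergency visits as well as readmissions.
- **Blinding and Allocation Concealment** defines the single blinding: "Statisticians will assess the primary and secondary outcomes, blinded to the randomization group". It adds that "neither the patients nor the care providers will be blinded to the randomization". The abstract also places the blinding at analysis: "A blinded independent research team will analyze outcomes".
- **Data Collection** assigns cancellations to one research team member working from the hospital record. When the day-30 form is missing or incomplete, "patients will be called by one of the research assistants" to obtain the indicators. A patient whose form reports an event is also telephoned. Masking is not mentioned for any of these people.
- **Control Group** gives both arms the same forms at days 15 and 30. **Data Collection** adds cross-referencing with the hospital's own record system.

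**The concern.** Each causal condition is a judgement made from a chart note, a form answer or a telephone conversation. Patients and care providers know the arm, so what they report or write down may reflect it. Nothing stated keeps the arm from the staff who extract and call. A statistician who is blind to arm but works on events already selected by cause cannot recover those left out, or remove those wrongly let in.

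The cancellation condition is especially exposed. Whether instructions were followed is what the platform is meant to improve, because the intervention arm receives them again the day before surgery. A belief about the platform could therefore colour the recorded reason for a cancellation.

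At stake is whether a difference in cost between arms reflects fewer events or a different way of finding and labelling them. That matters for a trial meant to inform public funding decisions.

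**Working it through.** **1. Where cause is judged and where blinding applies**

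| Step | Who, as stated | Masking stated? |
|---|---|---|
| Patient reports an event on a form | Patient | No; knows the arm |
| Reason for cancellation is written in the record | Not stated; presumably care staff | Care providers know the arm |
| Cancellations extracted from the record | One research team member | Not stated |
| Missing or incomplete day-30 indicators obtained by telephone | Research assistant | Not stated |
| Reported event followed up by telephone | Not stated | Not stated |
| Outcomes assessed and analysed | Statisticians | Yes |

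The article does not say who decides that an event is related, or at which step. The declared blinding is placed at the last row, while the information on which cause is judged is produced in the rows above it.

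**2. Reach of the existing safeguards**

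Identical forms put the same questions to both arms. Cross-referencing can confirm that an event took place at this hospital, but not necessarily why. Table 1 lists calls to the provincial line and visits to family doctors or walk-in clinics under platform assessments, so these rest on patient report.

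**3. Illustration of size, with no true effect**

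Inputs from the Introduction: a same-day cancellation rate of 8% to 10% (midpoint 9%), and 60% of cancellations avoidable with better preoperative support. The 60% is an avoidable share, used here only as a proxy for the share attributed to unfollowed instructions. The attribution shift between arms is an assumption.

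Counted rate = cancellation rate × share attributed.

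- Control: 0.09 × 0.60 = 0.054, or 27 of 500.
- Intervention, 10-point shift: 0.09 × 0.50 = 0.045, or 22.5 of 500. Ratio 0.833, a spurious 17% relative reduction.
- Intervention, 5-point shift: 0.09 × 0.55 = 0.0495. Ratio 0.917, a spurious 8% reduction.
- Shift reversed (control 50%, intervention 60%): 4.5% v 5.4%, a spurious 20% relative increase.

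The ratios do not depend on the base rate. At 8% the 10-point shift gives 4.8% v 4.0%; at 10% it gives 6.0% v 5.0%.

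**4. Chance of a false significant result on one component**

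Use a two-sided 0.05 pooled test of two proportions, 500 per arm with no losses, and no true effect. Let the intervention arm's counted events be multiplied by an assumed ratio r, so p_T = r × p_C. The probability of a significant difference favouring the platform is Φ{[(p_C − p_T) − 1.96·SE₀]/SE₁}, where SE₀ is the pooled and SE₁ the unpooled standard error.

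| Component (control rate) | r = 1 | r = 0.9 | r = 0.8 | r = 0.7 |
|---|---|---|---|---|
| Emergency returns (9.4%) | 0.025 | 0.075 | 0.186 | 0.376 |
| Readmissions (7.3%) | 0.025 | 0.066 | 0.152 | 0.300 |
| Cancellations counted (10% × 60% = 6.0%) | 0.025 | 0.060 | 0.131 | 0.252 |
| Cancellations counted (8% × 60% = 4.8%) | 0.025 | 0.055 | 0.112 | 0.209 |

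The 9.4% and 7.3% come from the Introduction; every r below 1 is an assumption. With r = 1 there is no inflation. With r above 1 the bias runs against the platform. These are single event components, not costs: the article gives no unit costs, so a false cost difference cannot be computed.

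**The case against.** The other side has real points.

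- **Silence in a condensed article.** Call scripts, attribution criteria and masking of callers may be in the full protocol or a manual. This stands as to detail, and their absence is not the point. But the article does state its blinding rule, twice, and both times attaches it to assessment by statisticians or to analysis. As stated, the rule does not reach the people who gather the information on cause.
- **The collectors may be blind in practice.** A reader might infer that extractors and callers know the arm. The documents do not say so; they state no masking for them. Nor do they rule out that the statisticians apply the causal conditions themselves, although they would then still rely on what others recorded.
- **Direction.** A reader might infer a bias in favour of the platform. That is not supported. Daily prompts for four days and nurse contact after alerts could equally raise the reporting, or the labelling as surgery-related, of events in the intervention arm.
- **Reach of the condition.** Read alone, Primary Outcome may attach relatedness only to readmissions and medical visits. Extending it to calls and emergency visits depends on Data Analysis.
- **Existing checks.** It would be wrong to say that there are none. Identical forms are the main source apart from cancellations, and telephoning is limited to missing or incomplete day-30 forms and to reported events.
- **Definition narrower than the hypothesis.** The first hypothesis is to "reduce the rate of unanticipated cancellations of elective surgeries", with no condition on cause. However, it names better information and communication as the mechanism, and restricting an economic outcome to related costs is defensible. I do not treat this as an error.
- **Base rate.** Population excludes last-minute postponements after randomization, so the cancellation rate that reaches the analysis is uncertain. This limits the illustration, not the argument.

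**Conclusion.** The concern holds as a risk of bias of unknown size and direction. The primary outcome contains causal judgements, the declared blinding stops short of the people who collect the information for them, and the existing checks are partial. Blinded analysis cannot repair a difference in attribution or ascertainment that arose earlier.

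The 5.4% v 4.5% example shows only that a moderate shift can produce a visible difference from nothing. It rests on an assumed 10-point shift and a proxy share. It is not an estimate of what will happen, and it says nothing about the size of any false cost saving. If collection and attribution are in fact the same in both arms, there is no bias from this source. The point merits a change because the remedy is cheap; it does not invalidate the design.

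**What to change.** Keep the primary definition and make two changes.

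1. State that the existing staff who extract cancellations, attribute cause and telephone patients work without access to allocation. They should use one call script and one set of written criteria in both arms.
2. Pre-specify a sensitivity analysis counting every unanticipated same-day cancellation and every unplanned contact, visit and readmission within 30 days, whatever the cause. Take hospital events from the record system, and outside events from the forms where the wording captures them.

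**Cost.** Hide the allocation field from current staff, write a short criteria sheet, and run one further analysis. No new staff are needed. Some patients will reveal their arm during the call, and all-cause costs are noisier. Table 1 lists visits and readmissions without a condition on cause, but those are only row labels. If the forms ask only about surgery-related events, a small change in wording is needed, and patients already enrolled (142 by 31 October 2022, of 1000 planned) may lack all-cause data on outside events.
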